### Data analysis

All statistical analyses will be performed using SPSS (version 20, IBM, NY, USA). Descriptive statistics will be used to characterise demographic, clinical and laboratory variables. Distributions of primary and secondary outcomes will be examined using histograms and box plots for evidence of deviation from a normal distribution. If the distribution of a continuous outcome variable shows skewness or other marked departure from normality, mathematical transformations will be applied before using inferential techniques that require normality or alternative non-parametric methods (for example, bootstrap). An intention-to-treat analysis will be used to measure change in BMI SDS over time between the two groups and data will be adjusted for baseline age, BMI and gender.

### Data monitoring

A data monitoring committee will insure oversight of the trial and will meet with the principal investigator quarterly. This will provide independent review as to whether study participants are being exposed to unreasonable risks and will monitor study progress and integrity. The data monitoring committee will meet to review data from the ongoing trial (outcome data and data regarding adverse events) and make recommendations to the trial steering committee. Data will be managed in accordance with Temple Street Children’s University Hospital and UCC data protection policies. Any identifiable information that is obtained in connection with this study will remain confidential and will be disclosed only with the participant’s permission or as required by Irish or EU law.

### Adverse events

At each visit, participants and their parents will complete an adverse events form in order to capture any unintended effects of the trial. Spontaneous reporting of adverse events will be possible by calling the study phone line.

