#### ***Phase 2 treatment***

Phase 2 is a maintenance phase. Upon completion of phase 1, participants return with their parents for three 3-monthly booster maintenance sessions over 46 weeks [4]. These sessions are aimed to encourage the family to continue with lifestyle change and to manage barriers to change.

In the current study, having completed phase 1 of treatment, participants will be randomised for phase 2 to either usual care or smartphone care.

The smartphone application incorporates evidence-based behavioural change tools such as self-monitoring, goal setting, and peer support. Evidence-based tips are sent to the user in the form of a text tip, a video tip or an image tip. The tips aim to increase the knowledge of the participant with regard to healthy eating, physical activity, physical fitness and sleep. The user is encouraged to engage in daily goal setting to increase physical activity level and sleep, increase water intake, reduce intake of sugar and fat and to increase intake of fibre, fruits and vegetables. In addition, the user is encouraged to monitor their progress by reviewing their goals daily and by entering their height and weight measurements (which are charted over time).

Those randomised to usual care will return for three booster sessions and for measurement of primary and secondary outcomes at 6 and 12 months. Those in the smartphone group will use the smarphone app and will return for measurement of outcomes at 6 to 12 months. Contact with the participants will be ensured throughout the study by monthly phone-calls from the principal investigator. See Figure 1.

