### Data collection and management

Primary and secondary outcome measurement will take place during initial baseline assessment, at 6 months and at 12 months. Participants who drop out of the trial will be invited to attend these follow-up visits for measurement. Data will be stored on password-protected firewalled computers, which are accessible only to members of our research team and those involved in managing the application software. Blood samples will be labelled with the patient’s initials and medical record number and stored in laboratories that are locked when not in use. With the permission of the participant (or parent/guardian), the blood samples and information collected during this research study may be stored indefinitely and used by our research group for future studies. Any information about individual participants derived from the additional studies will be kept confidential. The participant may at any time request that the blood samples be destroyed. When the results of the research are published or discussed in conferences, no information will be included that would reveal the identity of any participant unless their specific consent had been obtained. Data will be entered using double-data entry to assure quality control.

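### Adverse event forms are tied to visits, and usual care attends more often than the smartphone arm, so events are liable to be under-recorded with the app

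*Protocol article*

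**What the plan says.** The Adverse events section gives two routes for collecting events. The solicited one is a form: "At each visit, participants and their parents will complete an adverse events form in order to capture any unintended effects of the trial". The other is passive: "Spontaneous reporting of adverse events will be possible by calling the study phone line".

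The Phase 2 treatment section sets attendance after randomisation, and it differs by arm. For usual care: "Those randomised to usual care will return for three booster sessions and for measurement of primary and secondary outcomes at 6 and 12 months". For the smartphone arm: "Those in the smartphone group will use the smarphone app and will return for measurement of outcomes at 6 to 12 months". The Data collection and management section fixes the measurement times for everyone: "Primary and secondary outcome measurement will take place during initial baseline assessment, at 6 months and at 12 months". The boosters are described as follows: "participants return with their parents for three 3-monthly booster maintenance sessions over 46 weeks".

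Both arms also appear to receive a regular call: "Contact with the participants will be ensured throughout the study by monthly phone-calls from the principal investigator". The content of these calls is not described further.

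The Data monitoring section says that the committee reviews "outcome data and data regarding adverse events". The Data analysis section describes no between-arm analysis of adverse events.

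**The concern.** The only solicited collection of adverse events follows attendance, and attendance depends on the randomised arm. Followed literally, the rule has usual care asked about events more often than the smartphone arm. The smartphone arm would then have gaps of about five to six months between forms.

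The less closely questioned arm is the experimental one, in which minors are managed largely at a distance. A lower event count there could partly reflect fewer occasions to report. The committee meets quarterly and judges risk to participants from these data. With forms about half a year apart, roughly every other meeting would have no new solicited report from a given smartphone participant. The trial aims to show non-inferiority on BMI SDS, so a tolerability record that looks better than it is would add to the case for adopting the app. Events that were never elicited cannot be recovered once data collection is over.

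**Working it through.** The protocol gives no figure of its own on this point, so there is none to reproduce. The check is a count of attendances, followed by a simple capture model.

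**Inputs from the protocol.** Randomisation follows phase 1, at about week 6, and follow-up ends at month 12 (week 52). That leaves 52 − 6 = 46 weeks. Measurement is at 6 and 12 months (weeks 26 and 52) in both arms. Usual care also has three boosters, three months apart.

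**Assumptions.** The exact booster dates and the period that the form covers are not given, so both are varied. The smartphone arm's measurement wording (a range from 6 to 12 months) is read as the two time points in the Data collection and management section.

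**Step 1: is a booster a visit?** The rule says each visit, without qualification. The Assessment section calls the dietitian's appointment both a visit and a session within one paragraph, so calling boosters sessions does not exclude them. The Data collection and management section, however, speaks of follow-up visits when it means the measurement attendances. The plain reading includes boosters, but the text does not settle it.

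**Step 2: attendances after randomisation, if boosters count.**
- Smartphone: 2.
- Usual care, boosters at about weeks 19, 32 and 45: 3 + 2 = 5.
- Usual care, boosters at months 3, 6 and 9 (one coincides with a measurement): 4.
- Usual care, boosters at months 6, 9 and 12 (two coincide): 3.

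If captured events are proportional to the number of forms, the deficit in the smartphone arm at equal true rates is 1 − 2/5 = 60%, 1 − 2/4 = 50% or 1 − 2/3 = 33%.

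**Step 3: allow for recall.** Suppose that each form captures events from the preceding *w* weeks and that true event rates are constant and equal. Capture in an arm is then the number of weeks from 6 to 52 that fall within *w* weeks before some form, divided by 46. The ratio of smartphone to usual care is the ratio of weeks covered:

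| Usual-care attendances | *w* = 4 | *w* = 13 | *w* = 26 |
|---|---|---|---|
| 5 | 8/20 = 0.40 | 26/46 = 0.57 | 46/46 = 1.00 |
| 4 | 8/16 = 0.50 | 26/46 = 0.57 | 46/46 = 1.00 |
| 3 | 8/12 = 0.67 | 26/39 = 0.67 | 46/46 = 1.00 |

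The deficit is one minus the ratio: 33% to 60% at four weeks, 33% to 43% at thirteen weeks, and 0% at twenty-six weeks.

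**Step 4: if only measurement visits count.** There are two forms in each arm, the ratio is 2/2 = 1.00 and the deficit is 0%.

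No scenario puts more events on record in the smartphone arm than in usual care.

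**The case against.** A reader might infer that the trial's safety comparison is biased in favour of the app, by a third to 60%. The document does not support that, for four reasons.

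- The word visit is not defined in the adverse events rule. If it means only the 6- and 12-month measurements, the arms are equal.
- No between-arm safety comparison is described. The committee's task is to watch for undue risk and to monitor progress and integrity, so no planned test exists to be biased.
- A form at 6 months can ask about the whole period since the previous one, and with full recall the deficit is nil. A range of 33% to 60% leaves out zero. Its upper end also needs all five usual-care attendances on separate dates, which the protocol does not state.
- It would be wrong to say that the monthly calls are not used for adverse events. Their content is not described, and a journal article commonly leaves such detail to the full protocol.

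All four stand, and they make the concern conditional. They do not remove it. The article does state a collection rule, and applied as written alongside the arm-specific schedule, that rule solicits the smartphone arm less often. The phone line is open to both arms but relies on families to call. The calls could close the gap, but nothing in the text says that they elicit events.

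**Conclusion.** The point holds in conditional form. The protocol ties solicited adverse event collection to visits and schedules three to five attendances after randomisation in usual care against two in the smartphone arm. If forms are completed at boosters and recall over about six months is incomplete, events are liable to be under-recorded in the smartphone arm. That would favour the app in what the monitoring committee sees.

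The deficit at equal true rates lies between 0% and about 60%. Where it falls depends on three things that the document does not give: whether boosters count as visits, how far back the form reaches and how well families recall, and whether boosters coincide with measurements. The direction is the same wherever there is a deficit. The primary outcome, the sample size and the error rate are untouched.

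**What to change.** Change the adverse events rule so that the same form, covering the period since the last form, is given in both arms at common times. These are the 6- and 12-month visits, plus a short scripted set of questions in the monthly calls that the protocol already plans. Scheduled ascertainment is then equal by design.

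Base any between-arm summary of adverse events on these common contacts. Continue to record every event from boosters, the phone line or elsewhere, and show all of them to the committee, marked by source. The committee's own tables should not be limited to the common contacts, because its task is to watch for risk and it needs every report.

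The cost is call time and data entry. With 46 weeks after randomisation and 52/12 = 4.33 weeks to a month, there are 46/4.33 = 10.6 calls, so roughly ten short forms per participant. For 134 participants that is about 134 × 10 = 1,340 forms, all under the planned double data entry. No new visits or staff are needed. The protocol gives the trial status as recruiting, so the change can be made while data are still being collected.

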## Discussion

The results of the trial will be communicated to study participants, research collaborators, funders and the general public via a scientific publication and lay summary. The findings are expected to guide further development of a telemedicine system for the management of clinical obesity in adolescence. Ethical concerns specific to telemedical interventions have been considered such as the provision of web-enabled devices to minors, ensuring the security of patient data via online systems, and the use of devices in healthcare delivery which may expose a child to radio-frequency electromagnetic fields.

## Trial status

Recruiting.

## Abbreviations

BMI: body mass index; SDS: standardised deviation score; W82GO: Temple Street W82GO Healthy Lifestyles programme.
